**Treatment Week 2-4**

**(Visits 3, 4 and 5)**

- ALSFRS-R
- Concomitant drug history
- Vital signs
- Haematology tests (to include Full Blood Count (FBC), Erythrocyte Sedimentation Rate (ESR)
- Coagulation Tests (to include INR, APTT and PT)
- Biochemistry tests (to include Troponin I, C-reactive protein (CRP), Glucose, Calcium
- Urea and Electrolytes (U&Es), Liver Function Tests (LFTs)
- Quality of Life questionnaire (ALSAQ-40)
- Pregnancy test for WOCBP (Week 4, day 22 only)
- **Study Drug administration** (The time of study drug administration will be recorded at each visit. All doses must be given at within +/- 24 hours of the Day 1 Week 1 administration time
- Adverse event/Toxicity reporting
- Dynamometer test

**Treatment Week 5**

**(Visit 6)**

- ALSFRS-R
- Concomitant drug history

- Vital signs
- ECG
- Haematology tests (to include Full Blood Count (FBC), Erythrocyte Sedimentation Rate (ESR)
- Coagulation tests (INR, APTT and PT)
- Biochemistry tests (to include Troponin I, C-reactive protein (CRP), Glucose, Calcium
- Serum Creatine Kinase – Muscle, Brain (CK-MB)
- Urea and Electrolytes (U&Es), Liver Function Tests (LFTs)
- Quality of Life questionnaire(ALSAQ-40)
- Urinary p75ECD levels
- Neurofilament Light Chain (NfL) levels (collect 10mls of whole blood to allow for 4-5mls plasma for analysis)
- Collection of Exploratory Biomarker Blood Samples
- Lung Function Tests (Forced Vital Capacity (FVC)) ≥ 50% of predicted value for gender, height and age at screening
- Sniff Nasal Inspiratory Pressure (SNIP) Results must be recorded as the mean of three recordings
- Haematology tests (to include Full Blood Count (FBC), Erythrocyte Sedimentation Rate (ESR)
- **Study Drug administration** (The time of study drug administration will be recorded at each visit. All doses must be given within +/- 24 hours of the Day 1 Week 1 administration time
- Adverse event/Toxicity reporting
- Dynamometer test

#### Treatment Week 6, 7, 8

##### (Visit 7, 8 and 9)

- ALSFRS-R
- Concomitant drug history
- Vital signs
- Haematology tests (to include Full Blood Count (FBC), Erythrocyte Sedimentation Rate (ESR)
- Coagulation tests (to include INR, APTT and PT)
- Biochemistry tests (to include: Troponin I, C-reactive protein (CRP), Glucose, Calcium
- Urea and Electrolytes (U&Es), Liver Function Tests (LFTs)
- Quality of Life questionnaire(ALSAQ-40)
- **Pregnancy test for WOCBP (Week 8, day 50 only)**
- **Study Drug administration** (The time of study drug administration will be recorded at each visit. All doses must be given within +/- 24 hours of the Day 1 Week 1 administration time
- Adverse event/Toxicity reporting
- Dynamometer test

**Treatment Week 9****(Visit 10)**

- ALSFRS-R
- Concomitant drug history
- Vital signs
- Lung Function Tests (FVC)
- SNIP test
- Haematology tests (to include Full Blood Count (FBC), Erythrocyte Sedimentation Rate (ESR))
- Coagulation tests (to include INR, APTT and PT)
- Biochemistry tests (to include: Troponin I, C-reactive protein (CRP), Glucose, Calcium)
- Urea and Electrolytes (U&Es), Liver Function Tests (LFTs)
- Quality of Life questionnaire(ALSAQ-40)
- Dynamometer test

**Treatment Week 10****(Visit 11)**

- ALSFRS-R
- Concomitant drug history
- Vital signs
- ECG
- Haematology tests (to include Full Blood Count (FBC), Erythrocyte Sedimentation Rate (ESR))
- Coagulation tests (to include INR, APTT and PT)
- Biochemistry tests (to include: Troponin I, C-reactive protein (CRP), Glucose, Calcium)
- Creatinine Kinase
- Urea and Electrolytes (U&Es), Liver Function Tests (LFTs)
- Thyroid function tests
- Immunoglobulins
- Quality of Life questionnaire(ALSAQ-40)
- Urinary p75ECD levels
- Neurofilament Light Chain (NfL) levels (collect 10mls of whole blood to allow for 4-5mls plasma for analysis)
- Collection of exploratory biomarker blood samples
- Pregnancy test for WOCBP
- Dynamometer test
- **Study Drug administration** (The time of study drug administration will be recorded at each visit. All doses must be given within +/- 24 hours of the Day 1 Week 1 administration time)

**Prior to Week 11**

- **A formal review will be conducted to discuss patient eligibility to determine whether to continue treatment beyond 10 weeks. If a patient consents to continued treatment they will follow the below continuation of treatment visits. If a patient is not eligible/ does not want to continue treatment they will follow the follow up (observation period) schedule.**

**Treatment Week 11**

- Re-consent
- ALSFRS-R
- Concomitant drug history
- **Study Drug administration** (The time of study drug administration will be recorded at each visit. All doses must be given within +/- 24 hours of the Day 1 Week 1 administration time)
- Adverse event/Toxicity reporting

**Treatment Week 12-24**

- Concomitant drug history
- **Study Drug administration** (The time of study drug administration will be recorded at each visit. All doses must be given within +/- 24 hours of the Day 1 Week 1 administration time)
- Adverse event/Toxicity reporting

**Treatment Week 14**

- ALSFRS-R
- Concomitant drug history
- Vital signs
- ECG
- Haematology tests (to include Full Blood Count (FBC), Erythrocyte Sedimentation Rate (ESR))
- Coagulation tests (INR, APTT and PT)
- Biochemistry tests (to include Troponin I, C-reactive protein (CRP), Glucose, Calcium)
- Serum Creatine Kinase – Muscle, Brain (CK-MB)
- Urea and Electrolytes (U&Es), Liver Function Tests (LFTs)
- Quality of Life questionnaire (ALSAQ-40)
- Lung Function Tests (Forced Vital Capacity (FVC))  $\geq 50\%$  of predicted value for gender, height and age at screening
- Sniff Nasal Inspiratory Pressure (SNIP) Results must be recorded as the mean of three recordings
- Haematology tests (to include Full Blood Count (FBC), Erythrocyte Sedimentation Rate (ESR))
- Pregnancy test for WOCBP
- **Study Drug administration** (The time of study drug administration will be recorded at each visit. All doses must be given within +/- 24 hours of the Day 1 Week 1 administration time)
- Adverse event/Toxicity reporting
- Dynamometer test

**Treatment Week 15, 16, 17 and 18**

- Concomitant drug history
- **Study Drug administration** (The time of study drug administration will be recorded at each visit. All doses must be given within +/- 24 hours of the Day 1 Week 1 administration time)
- Adverse event/Toxicity reporting

**Treatment Week 19**

- ALSFRS-R
- Concomitant drug history
- Vital signs
- ECG
- Haematology tests (to include Full Blood Count (FBC), Erythrocyte Sedimentation Rate (ESR))
- Coagulation tests (INR, APTT and PT)
- Biochemistry tests (to include Troponin I, C-reactive protein (CRP), Glucose, Calcium)
- Serum Creatine Kinase – Muscle, Brain (CK-MB)
- Urea and Electrolytes (U&Es), Liver Function Tests (LFTs)
- Quality of Life questionnaire (ALSAQ-40)
- Lung Function Tests (Forced Vital Capacity (FVC))  $\geq 50\%$  of predicted value for gender, height and age at screening
- Sniff Nasal Inspiratory Pressure (SNIP) Results must be recorded as the mean of three recordings
- Haematology tests (to include Full Blood Count (FBC), Erythrocyte Sedimentation Rate (ESR))
- Pregnancy test for WOCBP
- **Study Drug administration** (The time of study drug administration will be recorded at each visit. All doses must be given within +/- 24 hours of the Day 1 Week 1 administration time)
- Adverse event/Toxicity reporting
- Dynamometer test

**Treatment Week 20-23**

- Concomitant drug history
- **Study Drug administration** (The time of study drug administration will be recorded at each visit. All doses must be given within +/- 24 hours of the Day 1 Week 1 administration time)
- Adverse event/Toxicity reporting

**Treatment Week 24**

- ALSFRS-R
- Concomitant drug history
- Vital signs
- ECG
- Haematology tests (to include Full Blood Count (FBC), Erythrocyte Sedimentation Rate (ESR))
- Coagulation tests (INR, APTT and PT)
- Biochemistry tests (to include Troponin I, C-reactive protein (CRP), Glucose, Calcium)
- Serum Creatine Kinase – Muscle, Brain (CK-MB)
- Urea and Electrolytes (U&Es), Liver Function Tests (LFTs)
- Quality of Life questionnaire (ALSAQ-40)
- Urinary p75ECD levels
- Neurofilament Light Chain (NfL) levels (collect 10mls of whole blood to allow for 4-5mls plasma for analysis)
- Collection of Exploratory Biomarker Blood Samples
- Lung Function Tests (Forced Vital Capacity (FVC))  $\geq 50\%$  of predicted value for gender, height and age at screening
- Sniff Nasal Inspiratory Pressure (SNIP) Results must be recorded as the mean of three recordings
- Haematology tests (to include Full Blood Count (FBC), Erythrocyte Sedimentation Rate (ESR))

- 
- Pregnancy test for WOCBP
  - **Study Drug administration** (The time of study drug administration will be recorded at each visit. All doses must be given within +/- 24 hours of the Day 1 Week 1 administration time Adverse event/Toxicity reporting
  - Dynamometer test

If after review, patients are eligible to continue treatment beyond 24 weeks up to a maximum of 48 weeks, they will repeat the treatment and assessment schedule week 11 – 24.

### 7.3 Assessments

#### 7.3.1 Blood chemistry and Haematology

The following blood tests will be performed at each visit. All safety assessments will be done in local laboratories at the investigative site.

| Biochemistry      | Blood test                                                                                                                                                                                                                                                                                                                           |
|-------------------|--------------------------------------------------------------------------------------------------------------------------------------------------------------------------------------------------------------------------------------------------------------------------------------------------------------------------------------|
| U&Es              | Sodium
Potassium
Urea
Creatinine
*Estimated Glomerular Filtration Rate (eGFR) (calculated by Cockcroft-Gault equation or alternative as per institutional practice – Appendix 6)                                                                                                                                         |
| LFTs              | Albumin
Aspartate transaminase (AST)
Alanine Transaminase (ALT)
Alkaline Phosphatase (ALP)
Bilirubin (direct and indirect if total is $\geq 30$ )
Gamma Glutamyl Transpeptidase (GGT)                                                                                                                                 |
| Other             | Serum Creatine Kinase-MB (CK-MB)
Troponin I (not tested after treatment week 24)
C-reactive protein (CRP)
Glucose
Calcium
Thyroid Stimulating Hormone (TSH) (not tested after treatment week 24)
Free Thyroxine (Free T4) (not tested after treatment week 24)
Immunoglobulin G (IgG)
Immunoglobulin M (IgM) |
| Haematology       | Blood test                                                                                                                                                                                                                                                                                                                           |
| FBC               | Haemoglobin
Platelets
Red Blood Cells
White Blood Cells
Haematocrit
Mean Cell Volume (MCV)
Mean Cell Haemoglobin
Neutrophils
Lymphocytes
Monocytes
Eosinophils
Basophils                                                                                                                            |
| Other             | ESR                                                                                                                                                                                                                                                                                                                                  |
| Coagulation Tests | INR
APTT
PT                                                                                                                                                                                                                                                                                                                    |

##### 7.3.1.1 Liver Chemistry Management

There are no liver-specific stopping criteria as such (although there are opportunities for an independent committee to review general safety data and, if necessary, advise the trial be stopped. In the event of

liver parameters deviating from the thresholds described in Appendix 5, follow instructions in that section.

Liver chemistry increased monitoring criteria have been designed to assure subject safety and evaluate liver event aetiology (in alignment with the FDA premarketing clinical liver safety guidance). <http://www.fda.gov/downloads/Drugs/GuidanceComplianceRegulatoryInformation/Guidances/UCM174090.pdf>

### 7.3.2 Physical examination/symptom assessment

All physical assessments will be performed by a suitably qualified medical practitioner/research nurse PRIOR TO ADMINISTRATION OF STUDY DRUG and shall include:

- Blood pressure
- Heart rate
- Pulse oximetry. Results of oximetry should be the average of three recordings
- Weight (kg) to allow for accurate dosing of IMP
- Height (at screening only)
- Body Mass Index (BMI)
- Body temperature
- Respiratory rate
- Adverse Event assessment/reporting
- Dynamometer test

### 7.3.3 Electrocardiogram (ECG)

- 12 lead electrocardiogram (performed prior to administration of study drug)

### 7.3.4 Lung Function Tests (performed prior to administration of study drug)

- Lung Function Tests (Forced Vital Capacity (FVC))  
Ventilatory support is indicated when the FVC is less than 50 per cent of predicted in many patients with respiratory muscle weakness therefore an FVC  $\geq 50\%$  of predicted value for gender, height and age is required for trial entry. FVC will also be measured at Week 12, Week 24 and 2 weeks after the end of treatment. Should patients continue treatment beyond 24 weeks, FVC will be measured as per the Schedule of Assessments
- Sniff Nasal Inspiratory Pressure (SNIP). Results must be recorded as the mean of three recordings and the same nostril used at baseline must be used for subsequent visits/assessments

### 7.3.5 Quality of Life (performed prior to administration of study drug)

- Amyotrophic Lateral Sclerosis Functional Rating Scale (Revised) (ALSFRS-R)
- QOL ALSAQ-40

Quality of Life assessments will be performed at treatment weeks (Weeks 1 – 10) and during follow up visits (Week 12, 16, 20 and 24). Should patients continue treatment beyond 10 weeks Quality of Life assessments will be performed as per the Schedule of Assessments.

All patients will be invited to provide data on Quality of Life in a single point long-term remote follow up visit conducted over an 8 week period starting in Quarter 1 of 2021.

### 7.3.6 Pregnancy testing

Urine pregnancy test for WOCBP  $\leq 7$  days prior the first dose of IMP and every 4 weeks during the study. Should patients continue treatment beyond 10 weeks urine pregnancy test for WOCBP will also be performed regularly as per the Schedule of Assessments.

## 7.4 Sample Collection

### 7.4.1 Blood samples

#### 7.4.1.1 Pharmacokinetic samples

For all patients, blood samples for the determination of ILB levels will be collected as detailed in the Schedule of Assessments in the study protocol.

Samples (plasma) for PKs should be collected from whole blood, collected in anti-coagulant-treated Vacutainer tubes (3.2% sodium citrate (blue-topped)). Serum should not be prepared.

Samples for ILB measurements should be sent (single/few batches) to:

Eurofins BioPharma Product Testing Munich GmbH  
[name]  
[name]  
[name]  
Germany  
[contact] (phone)  
[[contact]](mailto:[contact])

| Time Point                                   | Blood Sample Type | Volume of blood (ml) |
|----------------------------------------------|-------------------|----------------------|
| Pre-dose (30 minutes prior to ILB injection) | Blood Plasma      | 14                   |
| 30 minutes post-injection                    | Blood Plasma      | 3.5                  |
| 60 minutes post-injection                    | Blood Plasma      | 3.5                  |
| 120 minutes post –injection                  | Blood Plasma      | 3.5                  |
| 150 minutes post-injection                   | Blood Plasma      | 3.5                  |
| 180 minutes post-injection                   | Blood Plasma      | 3.5                  |
| 240 minutes post-injection                   | Blood Plasma      | 3.5                  |
| 360 minutes post-injection                   | Blood Plasma      | 3.5                  |

Please use the current version of the laboratory manual for further information.

The remaining PK samples should be stored in a -80°C freezer and will be shipped in batches for HGF measurement (exploratory biomarker) to the Neuregenix laboratory.

**7.4.1.2 NfL levels** (performed prior to administration of study drug)

- 10mls Whole Blood collected in EDTA-treated Vacutainer tubes (lavender/purple top) (to allow for 4-5mls plasma for analysis).

Samples should be stored in a -80°C freezer and will be shipped in batches to Sahlgrenska University Hospital, (Neurokemi lab), Gothenburg, Sweden

Please see the latest version of the laboratory manual for further information

**7.4.1.3 Exploratory Biomarker Blood Samples** (performed prior to administration of study drug)

Exploratory biomarker samples for:

- HPLC analysis of purines, pyrimidines, oxidative/nitrosative stress compounds (n = 60)
- HPLC analysis of fat-soluble vitamins and antioxidants (n = 60)
- HPLC analysis of amino acids and amino group-containing compounds (n = 60)
- Spectrophotometric analysis of lactate (n = 60)
- PBMC samples will be collected for analysis of change in phenotypic balance
- HGF release in plasma following ILB administration (ELISA from PK samples)
- Creatine kinase and Myoglobin from plasma as markers of muscle atrophy associated with ALS

Please see the latest version of the laboratory manual for further information.

| Samples               | Visit                                     | Blood sample type | Volume (ml) |
|-----------------------|-------------------------------------------|-------------------|-------------|
| NfL                   | Wk 1, Wk 5, Wk 11/12*, week 24, week 26** | Plasma            | 6           |
| Exploratory Biomarker | Wk1, Wk5, Wk11/12*, Wk24, Wk26**          | Serum             | 5           |
| Exploratory Biomarker | Wk1, Wk5, Wk11/12*, Wk24, Wk 26**         | PBMC              | 10          |

\*Week 11 if patients continue onto the treatment extension phase of the trial. Week 12 if patients are on end of treatment visit.

\*\* Patients who complete 24 weeks of treatment and do not continue on to further treatment will have an end of treatment visit week 26.

Please see Appendix 12 and the latest version of the laboratory manual for further information.

**7.4.1.4 Research Samples**

Any remaining blood samples at the end of the study will be shipped and stored at the Sponsor's biobank for use in future ethically and scientifically approved research in the UK or overseas; including genetic studies, research which may use animals or in vitro models, and research involving private or commercial companies.

Please see the latest version of the laboratory manual for further information.

#### 7.4.2 Urine Samples (performed prior to administration of study drug)

Where possible the first urine of the morning should be obtained for each patient for:

- Urinary p75ECD levels

Please see Appendix 12 and the latest version of the laboratory manual for further information

### 7.5 Dose Modifications

During the dosing period, if patients experience any adverse events the following criteria must be followed:

Table 2 Dose Modifications for Adverse Events

| CTCAE Grade | ACTION                                                                                                                  |
|-------------|-------------------------------------------------------------------------------------------------------------------------|
| Grade 1-2   | At the discretion of the treating clinician continue treatment                                                          |
| Grade 3     | The treating clinician should consider stopping study treatment at this point. Or omit dose until resolved to grade 1-2 |
| Grade 4     | Discontinue study treatment                                                                                             |

Definition of Grade – see NCI Common Terminology Criteria for Adverse Events version 4 (NCI CTCAE v4)

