#### 7.1.6 Patient Stopping Rules

Patients will have treatment of ILB stopped if any of the following prospective criteria are met during the treatment period:

- The patient experiences a Serious Adverse Event related to IMP
- If there is a decrease in ALSFRS-R score (>50%) compared to baseline
- If a patient becomes pregnant during the study treatment period
- Unacceptable toxicity – any adverse event which, in the investigators opinion, requires termination of the study drug
- Unforeseen events – any event which in the judgement of the Investigator makes further treatment inadvisable
- SAE requiring discontinuation of treatment
- If a patient requires an anticoagulant e.g Warfarin, Aspirin, Clopidogrel, any novel anticoagulants (NOAC)s or low molecular weight subcutaneous heparin during the clinical trial
- PTT or aPTT > 1.5 x ULN
- INR > 1.8 x ULN

Patients, who stop weekly dosing, will be invited to remain in the observational part of the study up to 24 weeks, to enable assessment of safety related measures. Patients that discontinue ILB and subsequently start or re-commence Riluzole therapy will also be invited to remain in the observational part of the study up to 24 weeks.

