## 7.8 Treatment Discontinuation

See Patient Stopping Rules and Trial Stopping Rules (see protocol page (xiv))

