### 8.1 Reporting Requirements

#### 8.1.1 Adverse Events

All medical occurrences which meet the definition of an AE (see Appendix 4 for definition) should be reported. Please note this includes abnormal laboratory findings including those that are not clinically significant.

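### For an ILB-related SAE of CTCAE Grade 1-3, section 7.1.6 requires treatment to be stopped while Table 2 and section 7.6 permit continuing or resuming, and nothing says which prevails

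*Protocol*

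**What the plan says.** Section 7.5 (Dose Modifications) opens Table 2 with "During the dosing period, if patients experience any adverse events the following criteria must be followed". The table sorts by CTCAE grade alone and does not distinguish serious from non-serious or related from unrelated events:

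- For events of Grade 1-2, dosing may go on if the clinician so decides.
- For events of Grade 3, the clinician is asked to think about a stop and is given an alternative: "Or omit dose until resolved to grade 1-2".
- For events of Grade 4, the instruction is to end ILB.

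Section 7.6 (Treatment Interruptions) leaves restarting after omitted doses to the treating clinician. It makes no exception for a patient who has met a stopping rule.

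Section 7.1.6 (Patient Stopping Rules), repeated in the synopsis, lists nine criteria and says ILB will be stopped if any one is met. The first is "The patient experiences a Serious Adverse Event related to IMP". It carries no grade.

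Section 7.8 (Treatment Discontinuation) consists of a cross-reference: "See Patient Stopping Rules and Trial Stopping Rules". It does not mention Table 2.

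**The concern.** The two sections use different axes. Table 2 uses severity grade; the relevant rule in 7.1.6 uses seriousness and relatedness. Appendix 3 says that severity and seriousness are different things, and it counts an unplanned precautionary admission as hospitalisation. A related SAE below Grade 4 is therefore an ordinary possibility, and both sections apply to it.

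Three things are at stake.

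- **Conduct.** A site working from 7.5 and 7.6 could resume a patient whom 7.1.6 requires to stop. Section 6.1.2 makes adherence mandatory and allows no waivers except for immediate safety concerns, so that site would be in breach of one section while acting within another.
- **A primary outcome.** Sections 2.3 and 12.2.1.3 report the number and length of interruptions and the number of discontinuations. The same event falls under one heading or the other according to which section was followed.
- **The extension.** Section 4.2 excludes anyone who has met a stopping rule and cites 7.1.6. A patient resumed under 7.5 and 7.6 could complete ten weeks, which is extension inclusion criterion 1, and already meet exclusion criterion 1.

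**Working it through.** The plan states no figure on this point, so the check is a comparison of text. Inputs: Table 2 in section 7.5, the restart provision in 7.6, the stopping rules in 7.1.6 and the synopsis, and the definitions in Appendix 3.

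| Event | Section 7.1.6 | Table 2, with 7.6 | Result |
|---|---|---|---|
| Related SAE, Grade 1-2 | Stop | May continue, at discretion | Required stop against a permission |
| Related SAE, Grade 3 | Stop | Consider stopping, or omit and later restart | Required stop against a permission |
| Related SAE, Grade 4 | Stop | Discontinue | Agree |
| Not a related SAE, Grade 1-3 | Stop only if another criterion is met, such as the investigator's judgement of unacceptable toxicity | At discretion | No conflict from the AE criteria |
| Not a related SAE, Grade 4 | No grade criterion; left to judgement | Discontinue | Lists differ, but both can be obeyed |

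The conflict is confined to the first two rows. In no row does one section require stopping while the other requires continuing, so a site that stops complies with both everywhere.

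**Precedence.** Neither 7.1.6 nor 7.5 cites the other, and 7.6 cites neither. Section 7.8 points only to the stopping rules, so the Grade 4 instruction in Table 2 is absent from the section that deals with discontinuation.

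**Size.** Section 3 plans 15 patients. One patient moved from interrupted to discontinued changes the discontinuation proportion by 1/15 = 0.067, or 6.7 percentage points. Section 1.2.4 says recruitment ended early. The number enrolled is not given; with n patients the shift is 1/n, which is above 6.7 points for any n below 15. This is the effect of one such event, not an estimate of how many there are.

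**The case against.** The strongest defence is that the texts can be read together. The Grade 1-2 row is discretionary and the Grade 3 row names stopping first, so a clinician can obey Table 2 and 7.1.6 at once by stopping. A rule written for related SAEs might naturally be taken to override a general table. The synopsis repeats the stopping rules, and both 7.8 and the extension exclusion refer to them, which suggests that they govern. The drug-quantity outcome is descriptive, with no decision threshold. Section 11 places the last treatment visits in March 2020, and section 1.2.4 says treatment ended for good, so an amendment now protects no future dosed patient.

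Most of this stands, and it limits the point. It does not remove it: the override has to be inferred, while the lead-in to Table 2 is mandatory, covers every adverse event and carves out nothing, and 7.6 adds an unqualified permission to restart.

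A reader might infer more than the documents support:

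- **That the two sections give opposite mandatory instructions.** They do not, as the comparison shows.
- **That 7.1.6 makes the stop permanent.** It says only that treatment is stopped; permanence would be an inference from the observational follow-up and the extension exclusion.
- **That the coagulation limits in 7.1.6 also collide with Table 2.** Section 8.1.1 does make abnormal laboratory values adverse events ("Please note this includes abnormal laboratory findings including those that are not clinically significant"), but the comparison needs CTCAE grade cut-offs, which the documents do not give.
- **That an unrelated Grade 4 event is a contradiction.** The stopping rules do not claim to be the only grounds for stopping, so the Grade 4 row merely adds one.

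**Conclusion.** The point holds in a narrow form. For an ILB-related SAE of Grade 1-3, sections 7.1.6 and 7.5/7.6 are unreconciled: one requires a stop, the other permits continuing or resuming, and no text sets the order between them. The interruption and discontinuation counts in a primary outcome then depend on which section was followed, by 6.7 percentage points per affected patient if 15 were enrolled and by more if fewer were.

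A reader might also expect the tolerability outcome to change. For related SAEs it does not. Criterion 1 of the intolerable-event definition in section 2.3 is met by association with an SAE, whether or not dosing is stopped. A Grade 3 related SAE qualifies either way, and a Grade 1-2 one fails the grade criterion either way. Extension eligibility is not ambiguous either, since exclusion 1 cites 7.1.6 directly; the difficulty is that a patient resumed under 7.5 and 7.6 would already be excluded.

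The conclusion rests on the wording and on Appendix 3 keeping seriousness separate from severity. The documents do not say whether any such event occurred. With dosing over, the practical weight lies mainly in classification and reporting. This should be corrected, but it is not among the most severe faults a plan can have.

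**What to change.** Reconcile the synopsis stopping rules with sections 7.1.6, 7.5, 7.6 and 7.8:

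1. State which text prevails when an event falls under both Table 2 and a stopping rule, and whether the restart provision in 7.6 applies to a patient who has met a stopping rule.
2. Have section 7.8 refer to both the stopping rules and Table 2.
3. Define how the resulting omissions and stops are classified in the interruption and discontinuation summaries, and apply that definition to events already observed.

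Which clinical rule should stand is for the sponsor and investigators to decide. The cost is a few sentences by amendment and a check of recorded dose omissions and stops against the agreed definition. No extra visits, tests or data are needed.
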